**Fig. 2 Fig2:**
[figure not shown]
Randomization flowchart. *Patient-Practitioner Orientation Scale questionnaire **Patient Activation Measure questionnaire

### Masking

It is not possible to mask the intervention in a study of this nature. Patients and the persons in charge of data analysis will be blind to the group to which each PCP will be assigned.

### Intervention

#### Control group

Professionals in the control PCPs will follow the standard training referred to in the training plans of the region where the PCP is located. The healthcare services for these regions provide ongoing training in the form of face-to-face group courses or online individual courses for healthcare professionals charged with the care of patients with chronic diseases.

#### e-MPODERA virtual COP intervention group

Professionals in the PCPs assigned to the virtual COP group will receive a link via email to register and start voluntarily participating in the e-MPODERA COP. e-MPODERA is a virtual knowledge-sharing COP based on a web 2.0 platform (http://dev.epract.net/community2/empodera). It will feature educational and gamified elements — including lectures, articles, newsletters, a resource bank, forums and virtual (video/teleconferencing) meetings — aimed at facilitating learning and transferring knowledge and experiences between participants. All researchers in the e-MPODERA group will be involved in developing the COP by providing updated content.

The platform structure and components will aim to respond to the needs and interests of professionals through a customized itinerary and different levels of depth (approaches to challenges, problem solving, cooperation among participants, feedback). The intervention will propose that participants identify and apply tools and knowledge models and a moderator/facilitator (community manager) will ensure proper functioning of the platform. To design activities, a competence framework will be used that covers core competences and includes learning objectives. We will progressively include 3 thematic areas related to patient empowerment: health literacy, self-care (health knowledge, self-efficacy, behavioural change, lifestyle change, sign/symptom monitoring, technical skills, acceptance of the chronic disease) and shared decision-making (autonomy and self-determination). We will address the following topics: (1) strategies and tools to empower patients with chronic diseases (rating scales, diagnostic tools and improving ability to understand patient information); (2) the impact on outcomes of empowering patients; (3) experiences and best practices of empowerment; and (4) barriers and facilitators, methods and approach models.

### Outcome measures

#### Primary outcome

##### Healthcare professional attitudes

Specific measurement: the PPOS questionnaire (Additional file 4), developed by Krupat et al. in 1999 [27] will be used: this is a validated self-administered questionnaire containing 18 items scored on a 6-point Likert scale (1–6) that has been demonstrated to have very good psychometric properties [12, 27]. Professionals are classified by the PPOS into 3 categories according to their patient-centeredness score: low (≤4.57), medium (>4.57 and < 5), or high (≥5) [27]. We will translate and adapt the PPOS instrument for Spanish using the forward and back-translation procedure and will validate it within the e-MPODERA trial.

Specific metrics: change from baseline

Methods of aggregation: we will measure the mean of the PPOS questionnaire score. Time points: we will measure the primary outcome at the individual level by administering the PPOS questionnaire at baseline and at 12 months.

#### Secondary outcome

##### Patient level of activation

Specific measurement: we will assess the patient level of activation with the PAM activation questionnaire (Additional file 5). The PAM activation questionnaire, which assesses activation in patients with chronic diseases, is the most widely used tool to measure patient engagement in self-care [31]. A short version of 13 items developed by Hibbard in 2005 [28] evaluates patient beliefs, knowledge and confidence in terms of a wide range of health-related behaviours. It uses a 4-point Likert-type scale (1–4) with a total score that is translated into a scale ranging from 0 to 100 (100 is the highest level of activation) to make interpretation easier. A version has been translated into Spanish and has been validated [32]. We will use the Insignia Health PAM® Survey (http://www.insigniahealth.com/products/pam-survey) in this project.

Specific metrics: we will assess change from baseline. Methods of aggregation: we will measure the mean of the PAM questionnaire score. Time points: we will measure the secondary outcome at the individual level by administering the PAM questionnaire at baseline and at 12 months.

### Additional measures

We will collect relevant demographic and medical data at baseline from the patients themselves or from the medical record and other administrative registers: (1) for primary healthcare professionals: age, sex, PCP, Spanish region, and professional profile (speciality, care setting and years of professional experience); and (2) for patients: type and duration (years) of the primary chronic disease, number of chronic diseases, age, sex, education level (illiterate, primary incomplete, primary complete, secondary complete or university), occupation, marital status (married, single, divorced or widowed), living circumstances (alone or accompanied), level of Spanish language comprehension (low, medium or high), and healthcare resource use (number of GP or nurse visits in the past year).

### Data collection, management and analyses

We will collect a mixture of professional and patient-reported data, using validated questionnaires for the primary and most of the secondary outcome measures. We will require each recruiting site to keep accurate and verifiable source notes regarding each participant’s inclusion and continued participation in the study. We will collect, transfer and store data in accordance with Good Clinical Practice (GCP) guidelines and data protection requirements. The e-MPODERA standard operating procedures (SOPs) and study data management plan will define the exact procedures for collecting, transferring, storing and quality-controlling study data.

We will perform descriptive and exploratory analyses, including cluster analyses according to participant baseline characteristics, using means and standard deviations for continuous variables and proportions for categorical variables. We will compare the two groups in terms of PPOS scores, PAM scores and descriptive variables. We will perform inferential analysis using the Mann-Whitney U test — with a 95% confidence interval — to compare across-group results in the PPOS and PAM tests in terms of score at 12 months from baseline.

We will perform a multilevel analysis of models for the main outcome (the PPOS test), where the response variable will be the difference between initial and final scores in the questionnaire administered to participating professionals and the explanatory variable will be the dichotomous intervention variable (1 = COP/0 = control). This model considers covariates such as age, sex and professional profile and also takes into account the random effect associated with the COP. We will use the propensity score to control for possible selection bias and enhance the accuracy of the model.

We will perform intention-to-treat analyses using the statistical software (http://www.R-project.org/) and PASW Statistics 18. We will use the last observation carried forward to impute missing data and will report analyses with and without imputation. We will inform participants that they can leave the study at any time. We will report missing data, if applicable, by categorizing the participants as follows: mistakenly randomized, did not receive the intervention, withdrew consent, crossed over, dropped out, did not adhere, lost contact or other reasons not specified [33].

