**Methods:**

This paper describes the protocol for a cluster randomized controlled trial. We will randomly assign 18 primary-care practices per participating region of Spain (Catalonia, Madrid and Canary Islands) to a virtual community of practice or to usual training. The primary-care practice will be the randomization unit and the primary healthcare professional will be the unit of analysis. We will need a sample of 270 primary healthcare professionals (general practitioners and nurses) and 1382 patients. We will perform randomization after professionals and patients are selected. We will ask the intervention group to participate for 12 months in a virtual community of practice based on a web 2.0 platform. We will measure the primary outcome using the Patient-Provider Orientation Scale questionnaire administered at baseline and after 12 months. Secondary outcomes will be the sociodemographic characteristics of health professionals, sociodemographic and clinical characteristics of patients, the Patient Activation Measure questionnaire for patient activation and outcomes regarding use of the virtual community of practice. We will calculate a linear mixed-effects regression to estimate the effect of participating in the virtual community of practice.

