### Sample size

We calculated the required number of primary healthcare professionals for the purpose of comparing two independent means, considering as significant a post-intervention mean difference of 0.2 points and a common standard deviation of 0.5 points in the PPOS questionnaire between the e-MPODERA virtual COP intervention and control groups [29]. Each group will need 100 professionals, assuming alpha error of 0.05 and power of 80%. Since we will randomize by clusters, we have adjusted the sample size to take into account the design effect. Considering an intraclass correlation coefficient of 0.03 and assuming an average size per cluster of five healthcare professionals, we obtained a design effect of 1.12 [30]. Given these assumptions and expecting 20% loss to follow up after 12 months, we calculated a sample size of 270 healthcare professionals (135 professionals per group). The recruited healthcare professionals will, in turn, recruit a total of 1382 patients (assuming 20% loss to follow-up), the number that is required to detect a mean difference between the two groups of 4 points in the Patient Activation Measure questionnaire (PAM) scale [28].

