### Randomization

We will perform allocation by clusters — with the PCP as the randomization unit — to minimize possible contamination effects among professionals. An investigator blinded to PCP identity and to baseline PPOS and PAM results will centrally perform randomization after professionals and patients are selected. This investigator will randomly assign 54 PCPs (nine pairs for each of the three regions, each randomly assigned a code) to either the e-MPODERA virtual COP group or the control group (27 PCPs per group) using Epidat 4.1 software (balanced group option). The unit of analysis will be the primary healthcare professional. To reach the necessary sample size, each professional will be required to recruit at least six consecutive patients. Figure 2 depicts a flowchart of the randomization procedure.

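### The only between-group analysis stated for PAM is a Mann-Whitney U test that ignores practice clustering; the same unadjusted test also stands beside the PPOS model

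*Protocol article*

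**What the plan says.** Under Randomization, the protocol article states "We will perform allocation by clusters", with 54 practices split 27 and 27. Under Sample size it accepts the consequence: "Since we will randomize by clusters, we have adjusted the sample size to take into account the design effect", using an ICC of 0.03 and five professionals per practice.

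Under Data collection, management and analyses, the between-group comparison is then described as follows: "We will perform inferential analysis using the Mann-Whitney U test". An interval at the 95% level is to accompany it. The stated purpose of the test is "to compare across-group results in the PPOS and PAM tests in terms of score at 12 months from baseline". No clustered version of the test and no adjustment for practice is mentioned.

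The next paragraph of that section adds a model for one outcome only: "We will perform a multilevel analysis of models for the main outcome (the PPOS test", with the professionals' change in score as the response. The model "takes into account the random effect associated with the COP". The abstract says "We will calculate a linear mixed-effects regression to estimate the effect of participating in the virtual community of practice" and does not name the outcome. PAM is measured on individual patients (Secondary outcome) and serves the stated secondary aim (Aim). No multilevel or otherwise cluster-adjusted analysis of PAM appears in the article.

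**The concern.** Patients are nested in professionals, and professionals in practices. The practice is what is randomised. A rank test on individuals treats every patient or professional as an independent piece of evidence, so it understates the variance of the between-group comparison whenever members of a practice resemble one another. The sample-size section assumes that they do.

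For PAM, the secondary aim would rest wholly on such a test. A chance difference between two sets of 27 practices could be reported as an effect on patient activation more often than the nominal 5%, and the Discussion intends to draw a conclusion about patient empowerment from this outcome. For PPOS the same test is also called inferential, although a multilevel model is given as well.

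**Working it through.** **Inputs from the protocol article.** PPOS difference 0.2, SD 0.5, alpha 0.05, power 80%, ICC 0.03, five professionals per practice, 20% loss, 270 professionals, 1382 patients (Sample size); 54 practices, 27 per group (Randomization). The ICC and SD of PAM are not stated, so the PAM ICC below is an assumption shown over a range.

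**Step 1: reproduce the plan's own figures.**
- Per group before inflation: 2 × (1.96 + 0.84)² × 0.5² / 0.2² gives 99 after rounding up; the plan says 100.
- Design effect: 1 + (5 − 1) × 0.03 = 1.12, as stated.
- 100 × 1.12 × 1.2 = 134.4, rounded up to 135 per group, so 270, as stated.

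The plan's sizing therefore does depend on a positive ICC at practice level.

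**Step 2: cluster sizes.**
- PPOS: 270/54 = 5 per practice; after 20% loss, 5 × 0.8 = 4.
- PAM: 1382/54 = 25.6 per practice; after 20% loss, 25.6 × 0.8 = 20.5.

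**Step 3: effect of ignoring clustering.** With m analysed per practice, DE = 1 + (m − 1) × ICC. A test that ignores this uses a standard error too small by a factor √DE, so the true two-sided type I error of a nominal 5% test is 2 × [1 − Φ(1.96/√DE)], and the correct interval is √DE times as wide.

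| Outcome | m | ICC | DE | True type I error | Interval should be wider by |
|---|---|---|---|---|---|
| PPOS | 5 | 0.03 (protocol) | 1.12 | 6.4% | 6% |
| PPOS | 4 | 0.03 (protocol) | 1.09 | 6.0% | 4% |
| PAM | 20.5 | 0.01 (assumed) | 1.19 | 7.3% | 9% |
| PAM | 20.5 | 0.03 (assumed) | 1.58 | 11.9% | 26% |
| PAM | 20.5 | 0.05 (assumed) | 1.97 | 16.3% | 40% |
| PAM | 25.6 | 0.01 (assumed) | 1.25 | 7.9% | 12% |
| PAM | 25.6 | 0.03 (assumed) | 1.74 | 13.7% | 32% |
| PAM | 25.6 | 0.05 (assumed) | 2.23 | 18.9% | 49% |

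**Step 4: check by simulation.** The Mann-Whitney test itself was simulated under the null with normal data, 27 against 27 practices allocated within pairs, 6000 runs.
- ICC 0: rejection rate 5.2% at both 5 and 20 per practice, so the excess below comes from clustering.
- PPOS at ICC 0.03: 6.8% with 5 per practice and 5.7% with 4. The simulation standard error is about √(0.064 × 0.936/6000) = 0.3 percentage points, so these agree with the formula.
- PAM with 20 per practice: 7.2%, 11.5% and 15.6% at ICC 0.01, 0.03 and 0.05. With 26 per practice at ICC 0.03: 13.7%. A separate run of 4000 at ICC 0.05 gave 15.1% with 20 per practice and 19.6% with 26, hence about 16–20% as the rounded range.

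**The case against.** **An article condenses the full plan, and the analysis plan is not shown.** That would excuse an omission. Here a specific test is named as the inferential comparison for PAM, and the model that could have replaced it is restricted to PPOS.

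**The abstract promises a mixed model.** It names no outcome, and the analysis section assigns the multilevel model to PPOS. It cannot be read with confidence as covering PAM.

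**The professional is the declared unit.** The Randomization section says "The unit of analysis will be the primary healthcare professional". Averaging PAM within each professional would reduce the cluster size but leave professionals clustered in practices.

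**The size for PAM is uncertain.** This stands. The only ICC in the article, 0.03, is for professionals. The ICC of a change score may be lower than that of a raw score, and allocation within region and pairs could offset part of the inflation; the simulation gives no credit for either. A reader might infer that false-positive PAM findings would be far more frequent than 5%. That depends on the assumed ICC: at 0.01 the figure is 7–8%.

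**PPOS already has a model.** This largely stands. A reader might infer two rival PPOS analyses from which the favourable one could be picked. The abstract and the analysis section together point to the mixed model as the main PPOS analysis, and the rank test can be read as a preliminary unadjusted comparison. What remains is that it is labelled inferential, and that the model's random effect is tied in words to the COP, not to the practice, which needs clarifying.

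**Twelve-month score or change?** A reader might also infer that the rank test uses the 12-month score although both outcomes are defined as change from baseline. The phrase "to compare across-group results in the PPOS and PAM tests in terms of score at 12 months from baseline" can equally mean change over 12 months, so no contradiction is shown.

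**Conclusion.** The point holds for PAM and is wrong as written: the only stated between-group analysis of the secondary outcome ignores the unit of randomisation. The direction, p-values too small and intervals too narrow, follows from any positive ICC. The size rests on an assumed practice-level PAM ICC, equal cluster sizes of about 20.5 to 25.6, and no allowance for extra similarity among patients of the same professional: about 7–8% at 0.01, 12–14% at 0.03 and 16–20% at 0.05, against a nominal 5%.

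For PPOS the consequence is small. On the protocol's own ICC the true error is about 6.0–6.4%, roughly one percentage point above nominal, and a multilevel model is planned. The request there is to state clearly which analysis decides and that its random effect is for practice.

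**What to change.** - **PAM:** specify an analysis that accounts for practice. One choice is a linear mixed model with a random intercept for practice (and for professional within practice if estimable), adjusted for baseline PAM. A cluster-adjusted rank test, or a permutation test that re-randomises practices, would equally cure the defect.
- **PPOS:** state that the mixed model with a random intercept for practice is the single primary analysis.
- **Mann-Whitney test:** drop the unadjusted version, or label it descriptive and report no inference from it.

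The cost is analysis wording only: no new data or extra participants. PAM intervals will be somewhat wider, by about 9% to 49% over the assumed ICC range of 0.01 to 0.05.

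### PAM is defined and sized as a mean difference, but its only stated inferential analysis is a Mann-Whitney test on an ambiguously worded score, with no model-based, cluster-aware estimate adjusted for baseline PAM

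*Protocol article*

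**What the plan says.** Four parts of the protocol article bear on PAM.

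- **Secondary outcome, Patient level of activation.** The metric is given as "Specific metrics: we will assess change from baseline" and the summary as "we will measure the mean of the PAM questionnaire score". On level and timing: "we will measure the secondary outcome at the individual level by administering the PAM questionnaire at baseline and at 12 months".
- **Sample size.** The 1382 patients, with 20% loss to follow-up allowed for, are the number "required to detect a mean difference between the two groups of 4 points in the Patient Activation Measure questionnaire (PAM) scale".
- **Data collection, management and analyses.** The inferential method for both questionnaires is the Mann-Whitney U test with a 95% confidence interval, used "to compare across-group results in the PPOS and PAM tests in terms of score at 12 months from baseline". The multilevel model in the next paragraph is stated for the main outcome, PPOS. Its response is the professionals' score difference. The section also promises means and standard deviations for continuous variables and a comparison of the arms on PAM scores.
- **Randomization.** "The unit of analysis will be the primary healthcare professional", with no exception for PAM. The Abstract says the same. It also announces a linear mixed-effects regression without naming the outcome.

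**The concern.** The secondary aim is the effect of the community of practice on patient activation. It is the stated reason for recruiting 1382 patients. The outcome definition and the sample size both point to a difference in means, in PAM points. The stated inference is a rank test, which does not target that quantity.

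Two further features weaken the analysis. The wording leaves open whether the 12-month score or the change is tested. Under neither reading is baseline PAM a covariate, although it is collected from every patient before randomization. In addition, the only model with a random effect is reserved for PPOS, so nothing stated for PAM allows for patients being grouped within professionals and practices.

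The trial could therefore report on its secondary aim without a properly supported estimate to set against the 4 points that justified the patient sample.

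**Working it through.** **1. The planned figure.** The 1382 cannot be reproduced, because the article gives no SD, intraclass correlation, alpha or power specifically for PAM. Borrowing the PPOS settings (alpha 0.05, taken as two-sided, and 80% power), it can only be solved backwards:

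- Evaluable per arm: 1382 × 0.8 / 2 = 552.8.
- Implied SD = 4 × √(552.8 / (2 × DE)) / (1.960 + 0.842), where DE is the design effect.
- With DE = 1, SD = 23.7.
- With an assumed intraclass correlation of 0.03 and 1382 / 54 = 25.6 patients per practice, DE = 1 + 24.6 × 0.03 = 1.74 and SD = 18.0.

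Whichever inputs were used, the stated target is a difference of means.

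**2. What each candidate analysis estimates.** Because arms are randomized, the expected difference between arms is the same for the 12-month mean, the mean change and the baseline-adjusted mean. All three can be set against 4 points. The Mann-Whitney test instead addresses the probability that a patient in one arm scores higher than a patient in the other. A location-shift interval attached to it equals a mean difference if the two distributions differ by a pure shift. The article does not state that assumption, and it is not guaranteed on a scale bounded at 0 and 100.

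**3. Precision from baseline PAM.** The correlation r between baseline and 12-month PAM is not given, so 0.3 to 0.7 is assumed, with equal variances at the two times. Variance relative to a comparison of 12-month means:

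| r | change: 2(1 − r) | baseline-adjusted: 1 − r² | adjusted ÷ change: (1 + r)/2 |
|---|---|---|---|
| 0.3 | 1.40 | 0.91 | 0.65 |
| 0.5 | 1.00 | 0.75 | 0.75 |
| 0.7 | 0.60 | 0.51 | 0.85 |

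Adjustment has the smallest variance on either reading of the test sentence. The ratios are for mean-based comparisons of independent patients. They only approximate what is lost with a rank test in a cluster trial.

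**4. Why the estimate must allow for clustering.** Expected evaluable patients per practice: 1382 × 0.8 / 54 = 20.5. For a standard Mann-Whitney test on individual patients, the approximate two-sided type I error is 2(1 − Φ(1.96/√DE)), with DE = 1 + 19.5 × ICC. Assumed ICCs of 0.01, 0.03 and 0.05 give DE of 1.19, 1.58 and 1.97, and error rates of 7.3%, 11.9% and 16.3% instead of 5%.

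**5. Illustration of power.** Assume SD 18, ICC 0.03, DE 1.58 and hence about 553 / 1.58 ≈ 349 effective patients per arm. Power for 4 points is then 83.5% on 12-month means. If adjustment reduces the variance in full, it is 92.4% at r = 0.5 and 98.4% at r = 0.7.

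**The case against.** The strongest reply is that the plan is less bare than it looks.

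- **Baseline may be used.** Read with the outcome definition, the test sentence may well mean change, and every baseline PAM then enters the analysis. This stands. A reader might infer that baseline PAM is wasted, but the documents support only that it is ignored on one reading and used less efficiently on the other.
- **An estimate may exist.** The test comes with a confidence interval, and group means and SDs will be reported. A reader might infer that the 4-point difference is never estimated. That goes too far, since a crude difference can be formed from the reported means. What is absent is a model-based estimate that allows for clustering, and a statement of what the interval covers.
- **The unit of analysis.** The professional can reasonably be taken as the unit for the primary outcome only, since PAM is said to be measured at individual level. That is a fair reading, and one added clause would settle it.
- **Detail belongs in an analysis plan.** Covariates and random effects are commonly left there. Here, however, the article names a test for PAM and assigns the model to PPOS, so the choice is stated rather than left open. The mixed model in the Abstract names no outcome, and the only model described in the Methods is for PPOS.
- **Change from baseline is a valid metric.** It is, in a randomized trial. Preferring baseline adjustment is a gain in efficiency, not the correction of a bias.

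**Conclusion.** The point holds in this form: the inference stated for PAM does not match the quantity that is defined and sized, the variable tested is ambiguous, and no model-based, cluster-aware estimate of the mean difference is planned. The primary PPOS analysis is not affected. This is a change that should be made to the sole secondary efficacy analysis.

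The size is illustrative. For an assumed r of 0.3 to 0.7 and ignoring clustering, baseline adjustment brings the variance to 0.91 to 0.51 of a 12-month-only comparison, or 0.65 to 0.85 of a change-score comparison. A reader might convert this into lost patients, for example 1382 × 0.8 = 1106 completers being worth 1106 × 0.75 = 830 at r = 0.5. The documents do not support such a headline, because it needs the 12-month-only reading, independent patients and a value of r that the article does not give. Nor is a power shortfall for PAM shown: on the assumed inputs above, power is 83.5% without any baseline adjustment.

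**What to change.** In Data collection, management and analyses, and in any separate analysis plan:

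1. Make the PAM analysis a patient-level linear mixed model for the 12-month score. Use arm, baseline PAM and region as fixed effects, with random intercepts for practice and for professional within practice.
2. Report the adjusted mean difference with its 95% CI and interpret it against 4 points.
3. Keep the Mann-Whitney test only as a labelled sensitivity analysis. State whether it uses the 12-month score or the change, and what its interval estimates.
4. In the Abstract and under Randomization, say that the professional is the unit of analysis for PPOS and the patient for PAM.

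The cost is a few sentences and a somewhat longer analysis script. Both PAM administrations are already scheduled in Table 1, so no new data are needed. The drawback is reliance on a model with distributional assumptions, which the retained rank test helps to check.

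### The sample size rests on the SD of a PPOS score but the main model analyses change from baseline, so the 80% power holds only if the pre-post correlation is about 0.5 or more; baseline PPOS should be a named covariate

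*Protocol article*

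**What the plan says.** The Sample size section of the protocol article sizes the trial on a comparison of two group averages. It does so "considering as significant a post-intervention mean difference of 0.2 points and a common standard deviation of 0.5 points". The SD is described as "a common standard deviation of 0.5 points in the PPOS questionnaire", so it belongs to the score and not to a change in the score. The section arrives at 100 professionals per group for 80% power at alpha 0.05. It then allows for clustering ("Considering an intraclass correlation coefficient of 0.03 and assuming an average size per cluster of five healthcare professionals"), which gives a design effect of 1.12, and for 20% loss, to reach 270 in total, 135 per group.

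The Primary outcome section sets the metric as change from baseline. The section on data collection, management and analyses follows this for the multilevel model: "the response variable will be the difference between initial and final scores in the questionnaire administered to participating professionals". The explanatory variable is the arm. Age, sex and professional profile are given as examples of covariates, and a propensity score is added whose variables are not listed. Baseline PPOS is not named. The section on professional and patient recruitment has every included professional complete PPOS before the practice is randomized.

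**The concern.** The trial is sized on one variable and analysed on another, and nothing in the article links the two. The variance of a change score depends on how strongly the baseline and 12-month scores correlate. With a weak correlation, subtracting baseline adds noise, and the planned analysis has less power than the 80% stated. With a strong correlation, it has more.

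There is also an efficiency question that does not depend on the correlation being low. A change score fixes the weight on baseline at 1, whereas a model with baseline as covariate estimates that weight from the data. The second is more precise for any correlation below 1. It also corrects for a chance difference in baseline PPOS between the arms, which can occur with 27 practices per arm.

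**Working it through.** **Inputs from the Sample size section.** Difference 0.2; score SD 0.5; alpha 0.05 (two-sided reproduces the stated figure, while one-sided would give 78 per group); power 80%; ICC 0.03; 5 professionals per cluster; 20% loss; 135 per arm.

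**Assumed, because the article does not give it.** The pre-post correlation r, shown from 0.3 to 0.7. Also assumed: equal SDs at both visits, an ICC of 0.03 that applies to the change and to the baseline-adjusted outcome as well, and no precision gained from the other covariates.

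**Step 1: reproduce the plan.** n per group = 2 × (1.96 + 0.84)² × 0.5² / 0.2² = 98.1, so 99; the t-based solution is 99.1. The article states 100. Design effect = 1 + (5 − 1) × 0.03 = 1.12. Total = 2 × 100 × 1.12 × 1.2 = 268.8, or about 270. The stated figures are reproduced, on the SD of a score.

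**Step 2: effective size at analysis.** 135 × 0.8 / 1.12 = 96.4 per arm. If the loss is applied as the article appears to apply it (135 / 1.2 = 112.5 retained), the figure is 112.5 / 1.12 = 100.4.

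**Step 3: SDs.**
- Change score: SD = 0.5 × √(2(1 − r)).
- Baseline-adjusted: SD = 0.5 × √(1 − r²).
- Ratio of variances: 2(1 − r) / (1 − r²) = 2 / (1 + r), which exceeds 1 for every r below 1.

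**Step 4: power** = Φ(0.2 / (SD × √(2/96.4)) − 1.96).

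| r | SD of change | Power, change score | Power, baseline-adjusted | Variance ratio |
|---|---|---|---|---|
| 0.3 | 0.592 | 65.1% | 82.9% | 1.54 |
| 0.4 | 0.548 | 71.8% | 85.8% | 1.43 |
| 0.5 | 0.500 | 79.3% | 89.4% | 1.33 |
| 0.6 | 0.447 | 87.4% | 93.5% | 1.25 |
| 0.7 | 0.387 | 94.8% | 97.3% | 1.18 |

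**Step 5: break-even.** The largest SD that still gives 80% power is 0.2 / (√(2/96.4) × 2.80) = 0.496. The matching correlation is r = 1 − (0.496/0.5)²/2 = 0.51. With 100.4 effective per arm it is 0.49. With no loss at all (135 / 1.12 = 120.5 effective) it is 0.39.

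**Step 6: what the change score would need.** For 80% power at r = 0.3, 138 per arm before inflation: 2 × 138 × 1.12 / 0.8 = 386.4, or about 387 in total. At r = 0.4, 118 per arm, or about 331 in total. The same inflation rule gives about 278 at r = 0.5.

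**Step 7: the floor with baseline in the model.** At r = 0 the adjusted SD is 0.5, and power is 79.3% with 96.4 effective per arm (80.9% with 100.4). It rises from there as r rises.

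**The case against.** The strongest objection is that the covariate list is open. The three variables are offered as examples, the propensity score's contents are not given, and a condensed article may leave the full list to the analysis plan. A reader might infer that the plan excludes baseline PPOS, or that the analysis is a wholly unadjusted change score. The text supports neither reading: baseline PPOS is unnamed, and other covariates are present. This part of the objection stands. It does not remove the point, because the article does fix the response and the primary metric, and these do not match the quantity used for sizing. The baseline value of the outcome is also the covariate most likely to matter, and it should not be left to a choice among examples.

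Second, r is unknown. If it is above about 0.5, the planned model exceeds 80% power even without baseline. This stands too, and it makes the shortfall conditional. The power figures also give no credit for the named covariates or the propensity score.

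Third, with randomization in pairs within region, the change-score estimate is unbiased on average. This is correct. Regression to the mean after a chance baseline imbalance affects the particular trial at hand and is not a systematic bias of the design.

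**Conclusion.** The mismatch is real: the sample size uses the SD of a score, the response is a change, and no correlation or SD of change connects them. On the assumptions listed in the working, the stated 80% power holds only if r is about 0.5 or more (0.49 to 0.51, depending on how the 20% loss is applied). At r = 0.3 it would be about 65%, and at r = 0.7 about 95%.

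A reader might infer that the trial is underpowered. The article does not support that, because it gives no value for r. What holds without knowing r is that, if baseline PPOS stays out of the model, the variance of the treatment estimate is 2 / (1 + r) times what baseline adjustment would give: 54%, 33% and 18% larger at r = 0.3, 0.5 and 0.7.

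A reader might also infer that adjustment secures the full 80% at any correlation. That is slightly too strong. With 135 per arm and 20% lost, the floor is about 79%.

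**What to change.** In the primary mixed model, name baseline PPOS as a prespecified fixed covariate. The response can be the 12-month score or the change; once baseline is in the model the treatment estimate is the same, so the stated primary metric need not be altered. Power is then about 79% or more at any r of 0 or above with the present 270 professionals, and it largely stops depending on an unstated correlation. Use baseline PAM likewise in any model fitted to PAM.

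The cost is one covariate in the model. Both baseline questionnaires are already completed before randomization, so there is no extra burden on participants and no change in sample size.
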